### Randomization

Following the baseline survey, women who consented to participate in the study were individually randomized into 1 of 2 experimental arms: an intervention arm or a control arm. The women were randomized to the intervention and control groups such that intervention assignment was balanced according to the following baseline characteristics: neighborhood or household cluster, distance to the nearest family planning clinic, number of living children, months since last live birth, current use of family planning, age of marriage, educational attainment, and household wealth. As part of the balancing process, strata by each combination of characteristic values were created and observations were assigned to their respective strata. Observations within each stratum were then individually randomized by the Principal Investigators in a 1:1 allocation to either the treatment or the control group using computer-generated randomization through STATA, version 13 (StataCorp). Block randomization was not used in this study. Following individual randomization, the IPA Malawi intervention team implemented the intervention to the participants who were randomized into the intervention arm.

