### Primary Outcomes

At the designated 1-year and 2-year follow-up periods, the entire study sample of women was resurveyed to create a panel of individual women in which each woman and household would be observed over 3 time periods. In each follow-up round, we collected survey data on a range of primary outcomes of interest, which include (1) contraceptive use, including changes in contraceptive prevalence, changes in method mix, and adherence to methods (compliance and discontinuation) and (2) fertility and birth spacing outcomes, including pregnancy status, parity, and time since the last birth.

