### Analysis Plan

Analysis of quantitative study data will be conducted using STATA and R (the R Project), where appropriate. A descriptive analysis will be performed for all variables, and unadjusted comparisons between experimental arms will be conducted. Descriptive statistics will be performed, including frequencies, means, and standard deviations. In addition, chi-square tests and one-tailed *t* tests will be used to examine associations in the data. A *P* value <.05 will be considered statistically significant for all statistical tests that are conducted. Given our hypotheses of the impact of our intervention on our key outcomes, one-sided hypotheses tests will be conducted for all our main analyses. Continuous variables will be tested for normality and nonnormal values will be categorized or transformed appropriately.

Our main econometric specifications will estimate the intent-to-treat (ITT) effect of our family planning intervention on fertility and other outcomes by directly regressing our outcomes of interest on a binary variable indicating receipt of the intervention. The main econometric specification for estimating the ITT effect of our family planning intervention is defined as follows:

where *Y_it_* is the outcome variable of interest for woman *i* in the period *t*=0,1,2 for baseline, 1-year follow-up, and 2-year follow-up, respectively; *T_it_* is an indicator of assignment to the treatment arm; *X_it_* is a vector of individual-level covariates that are controlled for in the analysis; *_i_* is the individual-specific fixed effect; *Y_i0_* is the baseline level of the outcome; and *ε_it_* is the error term. Here, the outcome variables of interest include immediate, intermediate, and long-term outcomes mentioned in the previous sections.

We will conduct several subgroup analyses to examine how the family planning intervention effects vary across particular subpopulations. Subgroups of interest include pregnant women, new mothers, women who have previously used family planning, women who expressed a desire to space or limit births at baseline, poorer women, and women with low educational attainment. In addition, we will estimate heterogeneous treatment effects for girls, older children, and high-parity households.

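### The main ITT model indexes its covariates by period and does not confine them to pre-randomization values, so it permits adjustment for variables the intervention may change

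*Protocol article*

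**What the plan says.** The Analysis Plan lists the terms of the main model. The outcome is taken "in the period *t*=0,1,2 for baseline, 1-year follow-up, and 2-year follow-up, respectively". For the treatment term, "T_it_* is an indicator of assignment to the treatment arm". For the covariates, "X_it_* is a vector of individual-level covariates that are controlled for in the analysis". The model also has a term that "is the individual-specific fixed effect", and "Y_i0_* is the baseline level of the outcome". The covariates are not named. The displayed equation is missing from the text available for this review, so the reading rests on this list of terms.

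Two other sections bear on what X could hold. Primary Outcomes describes a panel in which "each woman and household would be observed over 3 time periods". Randomization lists baseline characteristics used to balance the arms, among them "number of living children, months since last live birth, current use of family planning, age of marriage, educational attainment, and household wealth". The Analysis Plan also says that "unadjusted comparisons between experimental arms will be conducted".

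**The concern.** An ITT contrast compares the arms as randomized. Adjusting for covariates fixed before randomization keeps that contrast and usually sharpens it. Adjusting for a covariate measured after randomization keeps it only if assignment does not affect that covariate. Otherwise the coefficient mixes a partial effect, net of whatever runs through the covariate, with possible bias from unmeasured causes shared by the covariate and the outcome.

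Here the specification marks one term as baseline (Y_i0) and gives the covariates the running index. In a trial of family planning access, most of what is recorded again at years 1 and 2 is something the intervention is meant to change. This is the main model for contraceptive use, pregnancy, births and spacing, so the estimand of the primary results is at stake.

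**Working it through.** **1. Which covariates can act in the stated model.** An individual fixed effect is equivalent to subtracting each woman's own mean over periods. For a covariate fixed at baseline, X_i0 - mean over t of X_i0 = 0, so it vanishes. Y_i0 vanishes in the same way. Assignment survives only if T_it is coded 0 at baseline and 1 afterwards for treated women. Taken literally, the model therefore gives a role only to covariates that change after baseline.

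**2. What changes after baseline.** Table 2 lists as collected in both follow-up waves: family planning attitudes and knowledge, contraceptive use, pregnancy and fertility, anthropometry, education, employment, time use, income and expenditure, and assets. Primary Outcomes and Secondary Outcomes claim nearly all of these as outcomes. Age and interview date also vary and are harmless, but age advances almost equally for every woman.

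**3. Effect on the estimate.** Let the covariate be M = aT + gU + error and the outcome Y = cT + bM + hU + error, with U unmeasured and all variances 1. The total ITT effect is c + ab. The coefficient on T after adjusting for M is c - a·gh/(g² + 1). The coefficients below are assumptions chosen so that the total effect is -0.30. Simulation with 1460 women and 2000 repetitions agrees to within 0.001.

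| Covariate M | a, b, c, g, h | Adjusted estimate |
|---|---|---|
| Not affected by assignment | 0, -0.5, -0.3, 0, 0 | -0.30 |
| Affected, but unrelated to outcome | 0.3, 0, -0.3, 0, 0 | -0.30 |
| Carries half the effect | 0.3, -0.5, -0.15, 0, 0 | -0.15 |
| Carries all the effect | 0.6, -0.5, 0, 0, 0 | 0.00 |
| Acts in the opposite direction | 0.3, 0.5, -0.45, 0, 0 | -0.45 |
| Shares an unmeasured cause with outcome | 0.3, 0, -0.3, 1, 1 | -0.30 - 0.3 × 1/2 = -0.45 |

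The bias can thus be nil, toward zero or away from zero.

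**4. An example on the intended pathway.** Take the 6.5-point gain in use from the Contraceptive Prevalence section. Assume pregnancy risks of 8% in users and 40% in non-users, which the protocol does not give. The effect on pregnancy is 0.065 × (0.40 - 0.08) = 0.021, or 2.1 points. All of it runs through use, so adjusting for use at the same wave leaves zero, whatever the assumed gap in risk.

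**5. The plan's own power figures.** Table 4 (SD 2, 730 per arm, α = .05) reproduces one-sided. The standard error is 2 × √(2/730) = 0.1047 and power is Φ(d/0.1047 - 1.645). For d = 1.0, 0.5, 0.3 and 0.2 this gives 1.000, 0.999, 0.889 and 0.605, against the stated 1, 0.99, 0.89 and 0.61. These figures use no covariates, so they neither depend on X nor change if X is restricted to baseline.

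**6. Illustration of power.** Suppose adjustment removes a share m of the effect and the standard error stays the same (both assumptions):

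| m | d = 0.5 | d = 0.3 |
|---|---|---|
| 0 | 0.999 | 0.889 |
| 10% | 0.996 | 0.825 |
| 25% | 0.974 | 0.693 |
| 50% | 0.771 | 0.416 |
| 75% | 0.326 | 0.177 |

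If adjustment instead inflates the 0.3-birth effect by 25%, to 0.375, apparent power is 0.974, but for the wrong quantity. Nothing in the protocol fixes m.

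**The case against.** The case against is substantial. The period index proves little alone, because assignment carries it too although each woman is randomized once. The fixed-effect argument would equally remove Y_i0, which the authors include, so they may not have thought the absorption through. The balancing factors in Randomization are introduced as baseline characteristics, and nothing moves their follow-up values into X. Covariate choice is commonly left to an analysis plan, and Availability of Data and Materials mentions a preanalysis plan that is not shown. Unadjusted comparisons are planned as well.

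Much of this stands. A reader might infer that the trial adjusts for covariates measured at each wave instead of at baseline, that X contains mediators, and that the fertility effect will therefore be shrunk. The protocol supports none of these as fact. No covariate is named, and the direction depends on what X contains. Simulations that regress parity on living children at the same wave do show large losses, but that nearly regresses the outcome on itself and rests on assumed birth rates. It does not measure this plan.

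What does not stand is that nothing is wrong. The absence of a covariate list is not the point. The point is a stated main specification that indexes X by period, sets no pre-randomization limit, and includes a term that makes baseline covariates inert. Whatever the authors intended, following it literally leads toward post-randomization covariates. An unadjusted comparison alongside does not repair the estimand of the main model.

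**Conclusion.** The concern holds in conditional form. As written, the main ITT model permits adjustment for post-randomization variables, and with the individual fixed effect it gives a role to no others. If any variable affected by assignment and related to the outcome, directly or through a shared cause, enters X, the coefficient on assignment in general ceases to be the total ITT effect. The bias is toward zero for mediators on the intended pathway and may go the other way for other covariates.

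The size cannot be derived from the protocol. The figures above rest on assumed associations and show only the possible range, from no bias to loss of the whole effect or inflation by half (-0.45 against -0.30). The conclusion assumes that the term definitions in the Analysis Plan describe the model to be fitted. An unseen analysis plan that limits X to baseline would settle the matter of timing, though the article would still need to agree with it.

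**What to change.** - Replace X_it by X_i0, the values recorded in the baseline survey before randomization. The balancing factors in Randomization are natural candidates. A factor that is itself the baseline outcome need not be entered twice.
- Fit the model to the year 1 and year 2 outcomes, adjusting for Y_i0, and drop the individual fixed effect. Changing the subscript alone would not work, because the fixed effect would absorb both X_i0 and Y_i0.
- As time-varying terms, allow only survey wave and clearly exogenous timing variables such as age or interview date. Each follow-up round lasted about six months, so timing may be worth including.
- State that no year 1 or year 2 value of a variable the intervention could affect enters an ITT model.

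The cost is a short text change and slightly less freedom in choosing covariates. The baseline values are already collected, and the article reports no results. Because the follow-up data are in hand, the rule should be recorded before the primary analyses are completed.

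### As its terms are defined, the main intent-to-treat regression is internally inconsistent: a woman fixed effect absorbs both assignment and the baseline outcome, and no wave effect is named

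*Protocol article*

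**What the plan says.** The Analysis Plan section of the protocol article sets the aim: "Our main econometric specifications will estimate the intent-to-treat (ITT) effect of our family planning intervention on fertility and other outcomes". It says this will be done by "directly regressing our outcomes of interest on a binary variable indicating receipt of the intervention". The equation is missing from the text at hand, but the terms are defined beneath it:

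- Outcome, written `Y_it`, over three periods coded 0 to 2: "for baseline, 1-year follow-up, and 2-year follow-up, respectively".
- Treatment variable, written `T_it`: this term "is an indicator of assignment to the treatment arm".
- Covariates, written `X_it`: this term "is a vector of individual-level covariates that are controlled for in the analysis".
- One term, whose symbol is lost, "is the individual-specific fixed effect".
- Baseline value, written `Y_i0`: this term "is the baseline level of the outcome".
- There is an error term.

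No wave effect and no assignment-by-post term is defined. The Randomization section says that, after the baseline survey, "women who consented to participate in the study were individually randomized into 1 of 2 experimental arms". Each woman therefore has one assignment for the whole study.

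**The concern.** An individual fixed effect removes everything that is constant within a woman. Assignment is constant within a woman, and so is her baseline outcome. Putting all three in one model asks for coefficients that the data cannot supply. Counting baseline as an outcome period adds a second conflict, because `Y_i0` is then both a response and a regressor.

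An analyst would have to depart from the definitions to get an estimate, and the possible departures give different answers. One leans on the intervention arm's change over time, and another dilutes the effect. This is the model named for the primary outcomes, and the article says their analysis is still under way. The choice should not be left to whoever writes the code. The two names for the regressor add to the doubt, since receipt and assignment define different effects.

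**Working it through.** **Inputs.** From the article: three waves; individual randomization, once, after baseline; 730 women per arm at end line; modern contraceptive use of 19.5% against 26%, so a true effect of 0.065. Assumed for the simulations: complete data, a continuous approximation to the outcome, woman-level and residual SDs of 0.3 each, and the common time trends stated below.

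The plan states no figure that this model produces. Its power figure of 0.90 for 19.5% against 26% is reproduced (0.901, one-sided .05 with continuity correction). It concerns the end-line difference between arms and does not depend on this point.

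**1. The terms as defined.** Fixed-effects estimation subtracts each woman's own mean. For assignment `A_i` this gives A_i − A_i = 0 in every row, and for the baseline outcome Y_i0 − Y_i0 = 0. A rank check with 60 women over 3 waves agrees:

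| Design | Rank |
|---|---|
| Woman dummies | 60 |
| + assignment | 60 |
| + `Y_i0` | 60 |

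Neither coefficient is identified. This needs no assumption about trends or variances.

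**2. Treatment switches on after baseline.** Let T = A × post, with post = 0, 1, 1. Rank rises to 61, so the treatment coefficient is identified. Adding `Y_i0` leaves it at 61, so `Y_i0` is still absorbed. For an intervention woman the deviations of T from its mean are −2/3, 1/3, 1/3; for a control they are all 0. With no wave terms and no `X_it`, the coefficient is

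mean over intervention women of [(Y_1 + Y_2)/2 − Y_0] = τ + (r_1 + r_2)/2,

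where τ is the true effect and r_1, r_2 are the rises common to both arms.

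| Common rise, years 1 and 2 | Formula, τ = 0.065 | Simulation |
|---|---|---|
| 0, 0 | 0.065 | 0.065 |
| 0.05, 0.05 | 0.115 | not run |
| 0.10, 0.10 | 0.165 | 0.165 |
| 0.20, 0.20 | 0.265 | 0.265 |
| 0.40, 0.40 | 0.465 | 0.465 |
| 0.25, 0.35 | 0.365 | 0.366 |

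The bias equals the average common rise: 5 points for a 5-point rise, none for no rise.

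**3. Fixed effect dropped, t=0 kept, assignment constant.** Randomization makes the expected arm difference at t=0 zero. The coefficient averages over three waves: (0 + τ + τ)/3 = 2 × 0.065/3 = 0.043. Simulation gives 0.044, with or without wave terms. Reading the fixed effect as a random intercept does not remove this dilution, because the t=0 row remains.

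**4. Coherent forms** (rises 0.25 and 0.35, 500 data sets).

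| Model | Mean estimate | SD |
|---|---|---|
| Follow-up waves only: assignment, wave, `Y_i0` | 0.066 | 0.0155 |
| Woman fixed effects: assignment × post, wave, no `Y_i0` | 0.066 | 0.0191 |

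Both recover the effect. The variance ratio is (0.0155/0.0191)² = 0.66, in favour of the first. That ratio depends on the assumed SDs.

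**The case against.** The strongest reply is that the equation cannot be seen. The list beneath it defines no intercept and no treatment coefficient either, so it is not a complete inventory, and wave effects may be in the equation. The time subscript on `T_it` and the word receipt both suggest an indicator that turns on after baseline, which is identified. This stands as far as it goes: the documents do not prove that wave effects are absent. It does not rescue the text, because `T_it` is defined as assignment and `Y_i0` is absorbed under either reading of T.

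A reader might go further and infer that the model would return a huge spurious effect, about 40 points for a true 6.5, with the controls contributing nothing. The documents do not support that. The figure assumes control use of 19.5%, 50% and 59.2% over the three waves. The 50% has no source in the article. The 59.2% in Study Setting is national prevalence among married women of reproductive age, not modern use in this cohort. The figure also assumes that `X_it` is empty. On that same path, one covariate linear in time brings the estimate from about 0.41 to about 0.15. On a near-linear path (19.5%, 30%, 40%), adding age takes it from 0.211 to 0.064. With time-varying covariates in the model, controls do carry information. The plan's own Table 3 keeps controls at 19.5% at end line, which means no rise and so no bias of this kind.

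A reader might also infer from the subscript on `X_it` that the plan adjusts for parity or work measured after randomization. The Analysis Plan names no such covariate; the notation only leaves it open.

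Finally, unadjusted comparisons between arms are planned as well, and the powered contrast is the end-line difference. A badly biased regression would visibly disagree with them. That is a safeguard, but it does not make the main model coherent.

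**Conclusion.** The point holds as an internal inconsistency in the stated main model, not as a detail left for elsewhere. The absorption of assignment and `Y_i0` follows from the definitions alone.

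The numerical consequence depends on which repair an analyst would improvise. With treatment switching on after baseline and no wave effects, the bias equals the average common trend when `X_it` holds nothing that tracks time, and it may be smaller when it does. With the fixed effect dropped and t=0 kept, about one third of the effect is lost. Some common rise is plausible, because the women are pregnant or within 6 months of a birth at baseline and parity can only increase. Its size is not in the documents, so no single bias figure should be attached to this trial. The direct consequence is that the text does not determine which estimate would be reported as the main intent-to-treat effect.

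**What to change.** State assignment, not receipt, as the regressor, print the equation with every term, and choose one form:

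- **(a)** Waves t = 1, 2 only: assignment, wave effects, `Y_i0` and baseline covariates, with standard errors clustered on the woman and no woman fixed effect. This is generally the more precise.
- **(b)** Waves t = 0, 1, 2: woman fixed effects, assignment × post and wave effects, without `Y_i0`.

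Restrict adjustment covariates to baseline values. Under (b), fixed baseline covariates are absorbed and add nothing as main effects.

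The cost is a few lines of text and code; no new data are needed. Naming year 2 as the main estimate, adding an indicator for pregnancy at baseline, or keeping (b) only as a sensitivity analysis are reasonable preferences, but the correction does not require them.

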### Sample Size and Power Calculations

The sample size of this study was powered to primarily identify the effect of using family planning on fertility; however, we will also examine the effects of the intervention on other maternal and child health outcomes of interest, in addition to key social and economic measures of well-being. On the basis of the preliminary power calculations for our primary outcomes of interest, a total of 2000 women were needed to be enrolled in the study. Of the women who were enrolled, the family planning intervention, baseline survey, and 2 follow-up surveys were administered to 1000 women (the treatment group), whereas a basic family planning information package, the baseline survey, and 2 follow-up surveys were administered to the other 1000 women (the control group).

Our target baseline sample consists of 2000 women who met the eligibility criteria and who consented to participate in the study. Previous research studies in Accra, Ghana, have found that 32% of initially screened women either did not meet the eligibility criteria or refused to participate [20-22]. Therefore, to meet our target sample size of 2000, we would need to screen 3000 households if we conservatively assumed a combined ineligibility or refusal rate of 32% from the screening. Of the 2000 women who were to be recruited into the study at baseline following the initial screening process, 1000 women were to be randomly assigned to the intervention arm and the remaining 1000 women were to be randomly assigned to the control arm. On the basis of prior study findings from Zambia [13], we expected an attrition rate of 27% in the sample over a 2-year study period, which would leave us with an attrition-adjusted sample size of 730 women in each treatment arm, or 1460 women overall, at the end of the 2-year study period.

Given this attrition-adjusted sample size, we have powered our study to detect effects in 2 key outcomes, namely changes in contraceptive prevalence and fertility, the latter measured by the number of births per woman.

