### Contraceptive Prevalence

Using modern contraceptive prevalence estimates for Lilongwe from the 2010 Malawi DHS, we expect a modern contraceptive prevalence rate of 19.5% among women aged 18 to 35 years who are either currently pregnant or who are up to 6 months postpartum at baseline. To infer a potential effect size for our intervention, we look to evidence from (1) the Navrongo study in Ghana, which found that a family planning intervention with a comprehensive outreach and contraceptive delivery component increased contraceptive use by 6 to 8 percentage points over a 4-year study period and (2) the Matlab study in Bangladesh, which found far larger effects of contraceptive uptake among women in the intervention areas over a longer study period [9,23]. Our power calculations show that we will have 90% power to detect a 6.5 percentage point increase in the modern contraceptive prevalence rate in the intervention arm, from 19.5% to 26%, assuming that we will have an attrition-adjusted sample of 1460 women (730 women in each arm) at the end line.

Table 3 presents the levels of power 1-ß that will be achieved for various minimum effect sizes for modern contraceptive prevalence use (ie, the difference in the modern contraceptive prevalence rate between the intervention and control arms at end line), assuming a baseline contraceptive prevalence rate of 19.5 percentage points in both intervention and control arms and a fixed end-line sample size of 1460 women (730 in each arm).

**Table 3 table3:** Power calculations—contraceptive prevalence rate.

Control CPR^a^, n (%)	Intervention CPR, n (%)	Significance level, α	Control sample size	Intervention sample size	Power
142 (19.5)	190 (26)	.05	730	730	0.90
142 (19.5)	183 (25)	.05	730	730	0.79
142 (19.5)	175 (24)	.05	730	730	0.65
142 (19.5)	168 (23)	.05	730	730	0.47

^a^CPR: contraceptive prevalence rate.

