### Fertility (Number of Children Per Woman)

Similarly, we use fertility estimates for Lilongwe from the 2010 Malawi DHS and assume a baseline fertility rate of 4.5 births per woman in the sample at baseline. To infer a potential effect size, we again look to evidence from the Navrongo and Matlab studies, both of which found a total reduction of 1 birth per woman (equivalent to a 15% decrease in their respective baseline fertility) among women in their respective intervention arms over their respective study periods [9,23]. In recognizing that both the Matlab and Navrongo studies were larger-scale, cluster-randomized designs with longer follow-up periods, we estimate that we will only be able to observe differences of 0.5 births. Our power calculations show that we will have 99% power to detect a 0.5 birth per woman decrease, equivalent to a 12% decrease in fertility, in the intervention arm from 4.5 children per woman to 4.0 children per woman, assuming an attrition-adjusted sample of 1460 women (730 women in each arm) by end line.

Table 4 presents the levels of power 1-ß that will be achieved for various minimum effect sizes for fertility (ie, the difference in the average number of children per woman between the intervention and control arms at end line), assuming a baseline fertility of 4.5 children per woman in both intervention and control arms, a standard deviation of 2 children per woman for both arms, and a fixed end-line sample size of 1460 women (730 in each arm).

Finally, robustness checks (5% and 10% sample truncations and coarsening of independent variables) and falsification tests, which include placebo regression, simulation, and resampling methods, will be conducted to ascertain the strength and significance of our estimates. We will also conduct attrition-adjusted analyses to assess the extent of differential loss-to-follow-up outcomes.

**Table 4 table4:** Power calculations—fertility.

Control fertility, number of children per woman	Intervention fertility, number of children per woman	Significance level, α	Control sample size	Intervention sample size	Power
4.5	3.5	.05	730	730	1
4.5	4.0	.05	730	730	0.99
4.5	4.2	.05	730	730	0.89
4.5	4.3	.05	730	730	0.61

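### The protocol claims power for the effect of using family planning on fertility, but it powers and analyses the effect of assignment, and its 0.5-birth planning effect is not tied to the planned difference in use

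*Protocol article*

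**What the plan says.** Sample Size and Power Calculations names the quantity for which the trial was sized: "The sample size of this study was powered to primarily identify the effect of using family planning on fertility". The calculation rests on "an attrition-adjusted sample size of 730 women in each treatment arm, or 1460 women overall".

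The Analysis Plan describes a different quantity: "Our main econometric specifications will estimate the intent-to-treat (ITT) effect of our family planning intervention on fertility and other outcomes". The treatment variable in that model "is an indicator of assignment to the treatment arm". For the tests, "one-sided hypotheses tests will be conducted for all our main analyses", and a P "value <.05 will be considered statistically significant for all statistical tests that are conducted".

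Two power calculations follow, both for the same 730 women per arm at end line:

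- Contraceptive Prevalence (Table 3) claims "90% power to detect a 6.5 percentage point increase in the modern contraceptive prevalence rate in the intervention arm, from 19.5% to 26" per cent. The other rows of Table 3 are smaller (25%, 24% and 23%). The effect size is supported by a programme in Ghana that raised use by 6 to 8 points over 4 years, and by a second programme with larger effects, for which no figure is given.
- Fertility (Table 4) claims "99% power to detect a 0.5 birth per woman decrease", defined as a difference in mean children per woman between arms at end line, with SD 2. The 0.5 is scaled down from a reduction of one birth reported by the same two programmes.

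Study Objectives gives the primary objective as the impact of the intervention on contraceptive use, fertility, birth spacing and other outcomes.

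**The concern.** Women are randomised to an offer of services that they may decline, stop or resume. The effect of assignment and the effect of using contraception are therefore different quantities. The sample size section names the second, while the model, Table 4 and the objective concern the first.

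The two power calculations also stand side by side without a link. An intervention meant to improve access to contraception should lower births largely by raising or improving use. The arm difference in births then depends on how many more women use contraception and how many births each of them averts during follow-up. The protocol sets the 0.5-birth difference without reference to the 6.5-point difference in use.

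At stake is how a null result on births would be read. A reader who takes the sizing sentence and the printed 0.99 together could treat a null as strong evidence that using family planning does not reduce births. The design does not support that inference.

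**Working it through.** **Inputs from the protocol article.** 730 per arm, alpha .05, one-sided, SD 2 children, difference in use 0.260 − 0.195 = 0.065, follow-up 2 years.

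**Step 1: reproduce the printed power.** For Table 4, SE = 2 × √(2/730) = 0.1047 and one-sided power = Φ(difference/SE − 1.645).

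| Difference (births) | Computed | Printed |
|---|---|---|
| 1.0 | 1.000 | 1 |
| 0.5 | 0.999 | 0.99 |
| 0.3 | 0.889 | 0.89 |
| 0.2 | 0.605 | 0.61 |

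Two-sided values for the last three rows would be 0.998, 0.818 and 0.480, so the table is one-sided. Table 3 reproduces with a one-sided, continuity-corrected two-proportion test: 0.896, 0.794, 0.647 and 0.470, against 0.90, 0.79, 0.65 and 0.47 printed. Neither table contains an arithmetic error.

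**Step 2: link the tables.** Assume that the effect on births runs mainly through added modern use, and that end-line prevalence represents use over follow-up. Then

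arm difference in births = difference in use × births averted per added user.

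Solving for births averted per added user at 6.5 points:

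- 0.5 births: 0.5/0.065 = 7.7
- 0.3 births: 0.3/0.065 = 4.6
- 0.2 births: 0.2/0.065 = 3.1

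Randomization says that assignment was balanced on the number of living children. A difference in children per woman at end line should therefore come from births during the 2 years. Women entered pregnant or within 6 months of a birth, so even 3.1 averted births per added user is implausible. The smaller rows of Table 3 raise these figures (0.5/0.035 = 14.3). The top of the cited range lowers the first only to 0.5/0.08 = 6.25.

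**Step 3: power under the link.** The protocol gives no figure for births averted per added user, so 0.5 and 1 are assumptions. SD 0.5 is also an assumption. It represents the residual variation once baseline parity is accounted for, and gives SE = 0.5 × √(2/730) = 0.0262.

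| Births averted per added user | Arm difference | Power, SD 2 | Power, SD 0.5 |
|---|---|---|---|
| 0.5 | 0.5 × 0.065 = 0.0325 | 9% | 34% |
| 1 | 1 × 0.065 = 0.065 | 15% | 80% |

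At 8 points and 1 birth per added user, power with SD 2 is 19%.

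**Step 4: detectable difference.** At SD 2, 80% power needs (1.645 + 0.842) × 0.1047 = 0.26 births between arms. That is 0.26/0.065 = 4.0 births per added user, or a 26-point difference in use if each added user averts 1 birth.

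**The case against.** The case on the other side is substantial.

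- *The 0.99 is explicitly the power for an arm difference.* This stands. A reader might infer that true power is 9% where 99% is claimed. The documents do not support that, because the two figures answer different questions and Table 4 is correct for the one it asks.
- *The objective, model and Table 4 agree with one another.* This also stands. A reader might infer that the main model misses the trial's stated purpose. Study Objectives names the impact of the intervention, which is what the model estimates. The outlier is the sizing sentence.
- *6.5 points is a detectable difference, not a forecast.* True, so the two tables do not formally contradict each other. But it is the largest row shown, and a cited effect of 6 to 8 points supports it.
- *The same formula would reject the cited evidence.* One birth with 6 to 8 points gives 12.5 to 16.7 births per added user. However, the protocol equates one birth with 15% of baseline fertility, a baseline of about 1/0.15 = 6.7 births per woman. That is the scale of a lifetime fertility level. Part of the implausibility therefore comes from applying a fertility-level effect to a 2-year difference in children. This explains the gap without closing it.
- *Other pathways exist, and SD 2 may be too large.* Switching, continuation and management of side effects could add to the effect, and the model description includes the baseline outcome. Both points stand, and they are why a range is needed. If 20% of women were affected and each averted 0.5 births (assumed), the arm difference would be 0.10 and power at SD 2 about 24%.
- *An instrumental-variable analysis may be in an analysis plan that is not shown.* Agreed. Its absence from this article is not a fault.

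**Conclusion.** The point holds in a limited form. The claim that the sample was powered for the effect of using family planning has no calculation behind it. It conflicts with the main model, Table 4 and the stated objective, all of which concern assignment.

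Table 4 is numerically right for a difference between arms, but its planning effect is unsupported by the planned effect on use. If the effect runs mainly through added modern use, the largest planned difference in use would require 7.7 averted births per added user in 2 years, and 3.1 for the smallest row of Table 4.

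The power figures are conditional. For an assumed 0.5 to 1 birth averted per added user they are about 9% to 15% at the plan's SD and 34% to 80% at an assumed residual SD of 0.5. Only the most favourable of these combinations reaches conventional power. Because the assumed inputs move the result so much, none of these figures should be quoted as the trial's actual power. Randomisation and the validity of the intention-to-treat estimate are not affected.

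**What to change.** - In Sample Size and Power Calculations, describe the target as the effect of assignment to the intervention on fertility, and withdraw the claim of power for the effect of use.
- In the Fertility section, derive the arm difference as the planned difference in use times births averted per added user within follow-up. Use the SD that fits the baseline-adjusted outcome. Replace the single 0.99 with a range of power under stated assumptions.
- If an effect of use is reported, label it secondary and give its confidence interval.
- When reporting, do not present a null intention-to-treat result on births as evidence that use has no effect.

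The cost is wording and a recomputed power statement, with no new data or participants. Follow-up is complete, so the change affects interpretation and not design. The stated power for fertility will look less favourable over most of the range.
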